### Outcomes

The primary outcome of this study will be the salivary IgA levels of the children and will be reported in mg/100ml. The secondary outcome will be the pH levels of saliva in children. The primary and secondary outcomes will be assessed at the baseline, before any intervention, and after four weeks of intervention.

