### Sample size

To calculate the sample size, we used the following comparing two means formula (α=0.05, significance; $\beta \;=\;0.1;{\bar{x}}_{1}\;=\;1.4,\;{\bar{x}}_{2}\;\;=\;\;-3.1,S_{1}\;\;=\;\;4.1,\;\text{and}\;S_{2}\;\;=\;\;5.9$) based on the available literature (23) with maximum 30% falls during the follow-up, the final sample size was 40 participants per arm, 80 in total.

n=(Z(1−β)+Z(1−α/α22))2(S12+S22)(x¯1−x¯2)2

The participants will be selected using the convenience non probability sampling method. So, from the beginning of the study, any patient who meets the inclusion criteria and does not have the exclusion criteria will be selected and this process will continue until the sample size is reached.

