### Randomization and blinding

To limit the potential confounding effect of the age of the children, they will be randomly allocated to two groups. Participants will be randomized according to the method of block randomization in blocks of six using a computer-generated random number sequence. This process will be done by an independent statistician who will also give the sealed envelope of the treatment codes to the pharmacist in charge of the production of toothpastes. Each of the eligible patients accepted into the study will be assigned a number from a consecutive range. This number will then be sent to the pharmacist.

During the study, the participants, the outcome assessor, and the data analyst will be blinded and will not have access to the nature of the toothpaste the subjects will be testing. The product will be divided into opaque sealed bags and the labels will not show the difference between the postbiotic and the placebo toothpastes. In case of a serious and adverse event, the blind will be broken and the pharmacist will have access to the sealed envelopes.

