### Statistical analysis

The analysis of the data will be based on the intention-to-treat analysis and all recruited participants will be considered. Data normality will be examined using the Kolmogorov-Smirnov test. The variables will be reported as mean ± SD or median. The percentage changes for each variable will be calculated using the following formula in which *E* and *B* stand for the end value and the baseline value of the variable, respectively.

$$\left[\;\frac{E-B}{B\;\times \;100}\;\right]$$

In case of meeting the assumption of normality, the significant changes between the two groups will be evaluated using the independent t-test, otherwise, Mann-Whitney analysis will be used. Comparison of the mean of variables at baseline with that of post-intervention within each group will be conducted using paired *t*-test or Wilcoxon signed-rank test. In order to control any possible confounding variable, the analysis of covariance (ANCOVA) will be used when necessary.

All analyses will be performed using the Statistical Package for Social Sciences, version 22.0 (SPSS, Inc., Chicago, IL, United States) with statistical significance at *p *< 0.05.

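### The default between-group test is unadjusted and ANCOVA is optional with no stated trigger, so precision is lost and the deciding test is left open

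*Protocol article*

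**What the plan says.** The Outcomes section states: "The primary outcome of this study will be the salivary IgA levels of the children". IgA and the secondary outcome, salivary pH, "will be assessed at the baseline, before any intervention, and after four weeks of intervention". Every child should therefore have a baseline value of each, and Data collection adds age and gender.

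The Statistical analysis section defines a percentage change from baseline for each variable. It then tests changes between the groups by an independent t-test, or by Mann-Whitney if the data are judged non-normal. Its last word on method is: "In order to control any possible confounding variable, the analysis of covariance (ANCOVA) will be used when necessary".

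On age, Randomization and blinding says: "To limit the potential confounding effect of the age of the children, they will be randomly allocated to two groups". Allocation is in blocks of six, and no stratification by age is stated. The same section says that the data analyst is blinded.

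**The concern.** Two things are at stake.

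- **Precision.** In a randomised trial with a baseline measurement of the outcome, regressing the follow-up value on group and baseline is, in large samples, at least as efficient as a t-test on change. The data and the method are already in the plan, but the method is held in reserve.
- **The deciding analysis.** The article gives a rule for using ANCOVA, but the rule has no content: no trigger, no covariates, and no precedence if the t-test and ANCOVA disagree. The choice can then be made after baseline imbalance, or a first p-value, has been seen. The normality test that selects between t-test and Mann-Whitney is a further data-dependent step, though its direction is at least stated.

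**Working it through.** **Inputs from the Sample size section.** α = 0.05, two-sided (the formula uses the 1 − α/2 quantile); β = 0.1; means 1.4 and −3.1; SDs 4.1 and 5.9; and "maximum 30% falls during the follow-up, the final sample size was 40 participants per arm, 80 in total". A concentration cannot be negative, so the planning means must be changes from baseline.

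**Reproducing the plan's figure.**
- Difference = 1.4 − (−3.1) = 4.5.
- Sum of variances = 4.1² + 5.9² = 16.81 + 34.81 = 51.62; average SD = √(51.62/2) = 5.08.
- n = (1.2816 + 1.9600)² × 51.62 / 4.5² = 10.508 × 51.62 / 20.25 = 26.8, so 27 per arm.
- With 30% loss: 27 / 0.70 = 38.6, so 39 per arm against the stated 40. The figure reproduces, and it rests on an unadjusted comparison of changes.
- Completers at maximum loss: 40 × 0.70 = 28 per arm.

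**Variance ratio.** Let the SD be σ at both visits and the correlation between them r. The variance of a change is 2σ²(1 − r). The residual variance after regression on baseline is σ²(1 − r²). Their ratio is (1 + r)/2. The document does not give r; 0.3 to 0.8 is assumed.

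**Power at 28 per arm for a difference of 4.5** (noncentral t, two-sided 5%). For the change t-test the noncentrality is 4.5 / (5.08 × √(2/28)) = 3.31. For ANCOVA it is 3.31 / √((1 + r)/2).

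| Analysis | Variance ratio | Power |
|---|---|---|
| Change t-test | 1.00 | 90.2% |
| ANCOVA, r = 0.3 | 0.65 | 98.1% |
| ANCOVA, r = 0.5 | 0.75 | 96.4% |
| ANCOVA, r = 0.7 | 0.85 | 94.2% |
| ANCOVA, r = 0.8 | 0.90 | 92.9% |

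A normal approximation gives 91.2% for the change t-test and 93.7% to 98.4% for ANCOVA, in the same order. The ratio is a large-sample one. Estimating two covariate slopes with 56 children adds roughly 2/51 = 4% to the variance, so at r = 0.8 the ratio is nearer 0.90 × 1.04 = 0.94, which is still a gain. No gain is credited to age, because the document gives no relation between age and IgA.

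**Sample size with ANCOVA at 90% power.** 26.8 × 0.65 = 17.4, so 18 per arm; 26.8 × 0.90 = 24.1, so 25 per arm. After 30% loss: 18 / 0.70 gives 26 and 25 / 0.70 gives 36. Both are below 40.

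**False-positive rate** (simulation with no treatment effect, normal data, 28 per arm).
- Each test used alone: 4.9% to 5.6%, which is 5% within simulation error.
- The more favourable of change t-test and ANCOVA: 7.5% to 8.0% for r = 0.3 to 0.7 in one simulation, and 6.6% to 7.9% for r = 0.3 to 0.8 in another.
- With percentage change also available (assumed baseline coefficient of variation 0.2 to 0.3): 7.2% to 9.0%.
- ANCOVA used only when baseline IgA differs at p < 0.05, and the change t-test otherwise: 4.2% to 5.1% for r = 0.3 to 0.7.

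**The case against.** The strongest reply is that nothing here is invalid. Randomisation makes the unadjusted comparison of changes a sound test, the design reaches its 90% target, and a more efficient method is an improvement rather than a correction. That stands, and it limits the point to precision and to the open choice of test.

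It can also be said that covariate lists are commonly left to an analysis plan that is not shown. That is fair for the list alone. But the article does state a rule for ANCOVA, and that rule is conditional and undefined.

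The inflation needs selection on the result. The document does not say that this will happen, and a switch triggered purely by baseline imbalance would not inflate the error rate in the simulation above. Analyst blinding also makes steering towards a preferred arm harder. It does not stop an analyst who sees two coded groups and their p-values from deciding that adjustment is or is not needed.

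Three stronger readings are tempting, and the document does not support them:
- **That baseline IgA goes unused.** The section tests changes, and a negative planning mean can only be a change. Baseline is used, but not as a covariate.
- **That the false-positive rate is 10% to 13%.** This needs free choice among five tests, including a week-4 comparison that the section does not offer and a Mann-Whitney test that it ties to failed normality.
- **That chance imbalance in age damages the result.** No relation between age and IgA is given, so no effect on the estimate can be shown, and the test's error rate already allows for chance imbalance.

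**Conclusion.** The point holds as a matter of efficiency and pre-specification, not of bias or insufficient power. ANCOVA would cut the variance to 0.65 to 0.90 of that of the change score and raise power at 28 completers per arm from about 90% to 93-98%. These figures assume equal variances at the two visits, a correlation of 0.3 to 0.8, and planning SDs that are SDs of change; at the top of the correlation range the gain is only about 3 points. Leaving the deciding test open allows a false-positive rate of about 7-8%, or up to about 9% if percentage change is also in play, but only if the favourable result is the one reported. This should be changed before analysis; it does not threaten the trial.

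**What to change.** - State one primary analysis: ANCOVA of week-4 IgA on group, with baseline IgA and age in years as fixed covariates, reporting the adjusted difference and its 95% confidence interval. If IgA is skewed, fit the model on the log scale, and set that rule out in advance.
- Use the same model for pH, with baseline pH in place of baseline IgA.
- Delete the condition at the end of the ANCOVA sentence, so that adjustment does not depend on the data.
- Keep the t-test or Mann-Whitney on changes as a sensitivity analysis.

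The cost is wording only. The covariates are already collected, ANCOVA is already named in the plan, and the sample size of 80 is unchanged.

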### Monitoring

To maintain the accuracy and quality of the trial, and to check its compliance with the protocol, it will be monitored regularly by research associates. The findings of the trial monitoring will be reviewed by the Data Monitoring Committee (DMC).

### Adverse events

Since the study product will be in form of a toothpaste, minimal harm is expected. However, an adverse event (AE) has been defined as any unfavorable discomfort in the mouth during the study period. All the children and their parents will be advised to report any AE immediately and in case of AE, participant(s) will be excluded from the study.

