### Study product and intervention

The postbiotic strain *Bifidobacterium animalis subsp. animalis* PTCC1631 will be used. The intervention will be in form of a postbiotic-toothpaste (*B. animalis subsp. animalis, 10*^*9*^^*CFU*^/*g* (22)). The postbiotic strain was ordered from the Persian Type Culture Collection center, a subset of the Iranian Research Organization for Science and Technology. The postbiotic and placebo-toothpaste are similar in packaging, color, taste, and scent, and the only difference is the absence of the postbiotic ingredient in the placebo-toothpaste. Table 1 shows the ingredients of the toothpastes.

**Table 1 T1:** List of the ingredients of each toothpaste.

	Postbiotic-toothpaste (100 gr)	Placebo-toothpaste (100 gr)
*B. animalis subsp. animalis*	1–5 gr	
Sorbitol	30–40 gr	30–40 gr
Glycerin	20–30 gr	20–30 gr
Calcium carbonate	15–25	15–25
Carboxy methyl cellulose	1–2 gr	1–2 gr
Sodium saccharin	0.1–0.5 gr	0.1–0.5 gr
Sodium lauryl ether sulfate	2–5 gr	2–5 gr
Strawberry flavor	1–2 gr	1–2 gr
Distilled water	qs to 21 ml	qs to 21 ml

Eligible participants will be randomly allocated to two groups, intervention and control. The postbiotic-toothpaste will be given to the children in the intervention group and the children in the control group will receive the placebo-toothpaste. Children in both groups will be asked to brush their teeth twice a day (in the morning and at night) for two minutes, under the supervision of their parents, for four weeks. To eliminate any possible confounding effect of the method of tooth-brushing on the results, children and their parents will be instructed on how, when, and how long to brush their teeth at the beginning of the study.

In order to ensure participants adherence, parents will receive a message on a weekly basis to remind them the importance of tooth-brushing twice a day. Also, to motivate and encourage the children, they will be asked to record daily short videos of themselves while brushing their teeth and put it all together at the end of the four weeks.

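### The adverse event definition covers only discomfort in the mouth, so non-oral events and painless oral findings do not count as adverse events, and the unblinding trigger is not reconciled with it

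*Protocol article*

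**What the plan says.** The section on adverse events in the protocol article starts from an expectation: "Since the study product will be in form of a toothpaste, minimal harm is expected". It then fixes the definition: "an adverse event (AE) has been defined as any unfavorable discomfort in the mouth during the study period". Reporting and handling both depend on that term, since children and parents "will be advised to report any AE immediately and in case of AE, participant(s) will be excluded from the study".

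The only other mention of adverse events is in the section on randomization and blinding: "In case of a serious and adverse event, the blind will be broken and the pharmacist will have access to the sealed envelopes". That sentence neither defines a serious event nor refers to the definition above.

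The outcomes section names two outcomes and no harms outcome: "The primary outcome of this study will be the salivary IgA levels of the children", and "The secondary outcome will be the pH levels of saliva in children". On exposure, the section on the study product says "Children in both groups will be asked to brush their teeth twice a day", for four weeks, in children aged 6 to 12.

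**The concern.** The definition is narrow in two ways. It is limited to one body site, so a rash, vomiting, diarrhoea, fever or wheeze falls outside it. It is also limited to discomfort, so a painless lesion in the mouth falls outside it too. Because families are told to report adverse events, and the term has this meaning, the definition governs what is counted as well as what is labelled.

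The reason given is the form of the product, but the protocol's own rationale is not confined to the mouth. Its Discussion credits postbiotics with effects on diarrhoea, gastroenteritis, respiratory infection, cytokine production and T helper response. It also looks ahead to use of the paste as a preventive measure in children. A reader of the results will want to know what harms were seen in each arm, and a count on this definition would not answer that. A later analysis plan cannot restore events that were never collected.

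**Working it through.** **Is the definition widened elsewhere?** The sections that could do so were read side by side.

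| Section of the protocol article | What it adds on harms |
|---|---|
| Adverse events | The definition: oral, discomfort only; reporting tied to it |
| Randomization and blinding | A serious event breaks the blind; no definition, no body site |
| Eligibility criteria | Inflammatory disease, and medication or supplement use in the last two weeks or during the intervention, exclude a child; these are not called adverse events |
| Outcomes | Salivary IgA and pH only |
| Data collection | Medical history and medication at the start; outcomes re-evaluated at follow-up; harms not mentioned |
| Statistical analysis | No harms analysis |
| Monitoring | Regular monitoring, with findings reviewed by a data monitoring committee; no harms data specified |

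No section widens the definition.

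**How do the two mentions of adverse events fit together?** If the oral definition governs the unblinding sentence, a severe reaction outside the mouth does not meet the trigger. If it does not govern, the trigger has no definition in this document. The article does not say which reading holds.

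**The plan's own figure.** The article gives no figure on harms. The only design figure that bears on the illustration below is 40 per arm. From the sample size section: difference 1.4 − (−3.1) = 4.5; SDs 4.1 and 5.9; two-sided α = 0.05; power 0.90.

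- n = (1.960 + 1.282)² × (4.1² + 5.9²) / 4.5² = 26.8, so 27 per arm.
- With 30% loss: 27 / 0.7 = 38.6, so 39 per arm against the stated 40.
- The exact t-test needs 28 per arm, and 28 / 0.7 = 40.

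The stated 40 is therefore reproduced closely, and a wider adverse event definition does not change it.

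**Direction and illustration.** Let r be the true risk that a child has a reaction, and f the share of reactions that fall outside the definition. Among 40 children, the expected number counted is 40 × r × (1 − f). The chance of counting none is (1 − r(1 − f))^40. For any f above 0 the count falls and the chance of counting none rises, so the error has one direction. The values of r and f are assumptions; the article gives neither.

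| Assumed r | Assumed f | Expected reactions | Expected counted | Chance of counting none |
|---|---|---|---|---|
| 5% | 0 | 2 | 2 | 12.9% |
| 5% | 25% | 2 | 1.5 | 21.7% |
| 5% | 50% | 2 | 1 | 36.3% |
| 5% | 75% | 2 | 0.5 | 60.5% |
| 5% | 100% | 2 | 0 | 100% |
| 10% | 0 | 4 | 4 | 1.5% |
| 10% | 25% | 4 | 3 | 4.4% |
| 10% | 50% | 4 | 2 | 12.9% |
| 10% | 75% | 4 | 1 | 36.3% |
| 10% | 100% | 4 | 0 | 100% |

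Example: r = 5% and f = 50% give 1 − 0.05 × 0.5 = 0.975, and 0.975^40 = 0.363.

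**The case against.** The strongest reply is that nothing the plan sets out to estimate is affected. There is no safety objective, outcome, hypothesis or test, and the article makes future use conditional on effectiveness. That stands. A reader might infer that the trial's safety conclusion is biased, but the plan contains no such conclusion. What remains is that any harms statement made from these data would rest on an incomplete count.

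A second reply concerns unblinding. A reader might infer that no event outside the mouth could ever break the blind. The documents do not support that. The sentence on unblinding does not refer to the oral definition, and its natural reading includes a serious systemic reaction. The fault is an undefined term beside a narrow definition, not a rule that blocks unblinding.

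Third, a reader might infer that every non-oral event would go unrecorded. This is too strong. Applying the exclusions for inflammatory disease and for medication during the intervention means learning of some illnesses, and monitoring may bring others to light. These routes do not make such events adverse events, however, and they do not ensure a count by arm.

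Fourth, a reader might infer that collection is by spontaneous report only. The article describes no other route, but a condensed article may leave visit questions to the full protocol, so that inference rests on silence and is not part of this point. Leaving detail to another document does not excuse the definition itself, because the article states it outright.

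Lastly, the protocol describes the organisms as inanimate, and it does not say that paste will be swallowed. The point depends on neither matter.

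**Conclusion.** The point holds as a fault in a stated rule. Events outside the mouth and painless oral findings are not adverse events under the plan, and no other section corrects this. Any harms count would be too low or at best correct, never too high for this reason. The size is unknown: the tabulated figures rest wholly on assumed risks of 5% and 10%, assumed shares outside the definition, and all 40 children per arm being observed, whereas the plan allows for up to 30% loss. The narrow definition does not bias the IgA or pH comparisons, so this should be corrected but does not threaten the primary result. The definition and the unblinding trigger must be reconciled.

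**What to change.** In the section on adverse events, define an adverse event as any untoward medical occurrence at any body site, from first use of the paste to the week-4 visit, whether or not it is thought related. Define serious events separately, and state that those named in the section on randomization and blinding are not limited to the mouth. Add one open question on the child's health to the weekly message that parents already receive, and ask it again at the week-4 visit. Report adverse and serious adverse events by randomised arm.

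One sentence must be dealt with at the same time. The article excludes a child who has an adverse event, while its statistical analysis section promises intention-to-treat with all recruited participants considered. These passages already need to be reconciled. If the definition is widened and the exclusion sentence is left as it is, exclusion would reach more children, and the IgA and pH analyses would then be affected.

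The cost is a change of wording, one question in contacts that already take place, and slightly more event recording. Sample size and visit schedule do not change. The change is best made before data collection, because events that were not recorded cannot be recovered reliably afterwards.

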### Data collection

At the beginning of the study, demographic information (age and gender), medical history, accompanying medication, and any usage of antibiotics and probiotics will be recorded. The eligible subjects will be told not to eat or drink anything for one hour before the saliva collection. Afterwards, one ml of the unstimulated whole saliva of children will be collected into sterilized plastic test tubes using the spitting method between 9.00 and 12.00 a.m. under controlled temperature (23°C). The saliva samples will be kept at −80°C until they are sent to laboratory, where the levels of salivary IgA will be determined with enzyme-linked immunosorbent assay (ELISA) previously described in detail by Sonesson et al. (24). The 96 well-plates will be coated overnight by anti-human *α*-chain-specific IgA. The next day, the wells will be washed with Phosphate-Buffered Saline (PBS) containing 0.05% Tween-20 and blocked by 1% Bovine Serum Albumin (BSA) at 37°C for 1 h. Diluted saliva samples and standards will be incubated in wells for 1 h at 37°C. The wells will be washed and biotinylated anti-human IgA antibody will be added. After washing away unbound biotinylated antibody, HRP-conjugated streptavidin will be pipetted to the wells. The wells will again be washed, a TMB substrate solution will be added to the wells and color develops in proportion to the amount of IgA bound. The Stop Solution will change the color from blue to yellow, and the intensity of the color will be measured at 450 nm. The results will be plotted against a standard curve and multiplied with the dilution factor. Immediately after sample collection in order to prevent degradation of the saliva, pH analysis will be carried out using portable pH meter (Hanna Instruments®, HI98191, RI, United States) which will be calibrated with distilled water for each time of use. At the follow-up session, outcomes will be reevaluated accordingly. A trained pediatric dentist will collect all the data. Figure 2 presents schedule of enrolment, intervention, and assessments.

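### The only described route to adverse events is unprompted family reporting, and a report leads to exclusion, so harms are likely to be under-counted; an identical question at the two existing contacts would largely mend this.

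*Protocol article*

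**What the plan says.** The Adverse events section of the protocol article fixes three things.

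- Definition: "an adverse event (AE) has been defined as any unfavorable discomfort in the mouth during the study period".
- How events come to light, and the consequence of a report: the children and "their parents will be advised to report any AE immediately and in case of AE, participant(s) will be excluded from the study". It makes no distinction by severity or by relation to the product.

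Two contacts with families exist during the four weeks. Under Study product and intervention, "parents will receive a message on a weekly basis to remind them the importance of tooth-brushing twice a day". Under Data collection, "At the follow-up session, outcomes will be reevaluated accordingly". The Outcomes section names salivary IgA as primary and salivary pH as secondary, and says: "The primary and secondary outcomes will be assessed at the baseline, before any intervention, and after four weeks of intervention". No adverse-event question is described at either contact.

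Two other sections touch on safety or oversight. Randomization and blinding says: "In case of a serious and adverse event, the blind will be broken". Monitoring describes checks of quality and protocol compliance, with the findings reviewed by the Data Monitoring Committee. Neither describes a way of finding events.

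The Statistical analysis section states an intention-to-treat analysis that takes in everyone recruited.

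**The concern.** The described method depends on families with children aged 6 to 12 coming forward, unasked, about mouth discomfort that may be mild. Unprompted reporting tends to miss such complaints. A report then takes the child out of the study, so what happens after the first report may go unrecorded.

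Drop-out is a second way to lose events. The Eligibility criteria also exclude children who do not complete follow-up, and the Sample size section allows for up to 30% loss, which is 0.30 × 40 = 12 children per arm. A child who stops because of discomfort and does not return would leave without any described enquiry.

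What is at stake is how a low count would be read. The article expects little harm, and its Discussion foresees preventive use in children. A count of zero or near zero could mean good tolerability, silence or silent drop-out, and the data as described could not separate these.

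**Working it through.** **Does any section describe an active enquiry?**

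| Section | What it describes | Adverse-event enquiry described? |
|---|---|---|
| Adverse events | Families told to report | No, unprompted only |
| Study product and intervention | Weekly reminder; daily brushing videos for motivation | No |
| Outcomes; Data collection | IgA and pH at baseline and week 4 | No |
| Randomization and blinding | Unblinding after a serious event | No |
| Monitoring | Quality and compliance checks | No |

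The text is consistent: one route, and it is unprompted. Figure 2, the schedule of assessments, is not available here, so this holds for the text only.

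**Denominator.** The article gives no figure for adverse events, so the relevant number is its 40 per arm. From its own inputs (two-sided α 0.05, β 0.1, means 1.4 and −3.1, SDs 4.1 and 5.9):

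- n = (1.282 + 1.960)² × (4.1² + 5.9²) / 4.5² = 26.8, so 27 per arm
- 27 / (1 − 0.30) = 38.6, so 39 per arm, close to the stated 40

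**What zero reports in one arm would show.**

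- Full capture: the bound solves (1 − p)^40 = 0.05, so p = 1 − 0.05^(1/40) = 7.2%.
- Capture share c: the reported rate is c × p, so the bound on p is 7.2% / c.
- c = 0.5 (assumed): 14.4%.
- c = 0.3 (assumed): about 24%.

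These are upper confidence limits, not estimates of the rate.

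**Chance of seeing no event in 40 children**, (1 − c × p)^40, for assumed true rates and capture:

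| True rate | c = 1 | c = 0.7 | c = 0.4 |
|---|---|---|---|
| 5% | 12.9% | 24.0% | 44.6% |
| 10% | 1.5% | 5.5% | 19.5% |

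At a true rate of 10%, 40 × 0.10 = 4.0 affected children are expected per arm. With c = 0.4, 1.6 would be seen.

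**Effect on the arm comparison.** If c is the same in both arms, the expected reported rates are c × p₁ and c × p₀. Their ratio is unchanged, and their difference shrinks by the factor c.

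**Effect on power.** After 30% loss, 28 children per arm remain and power is 91%. If exclusions for adverse events of 5%, 10% or 20% (assumed) came on top of that loss, power would be about 90%, 88% or 84%. The larger cost is to the harms data and to the intention-to-treat set.

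**The case against.** The strongest reply is that this is a condensed article. It never says that unprompted reporting is the only route, the schedule figure is not available, and question wording or severity fields usually sit in the full protocol or case report form. That stands as a limit: the point is about the only route described, not about proof that no other exists. It does not remove the point, because the article goes beyond silence. It states a collection method and a consequence, and gives the content of both contacts without an enquiry.

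Second, parents are to supervise brushing twice a day, so an adult should be present at product use and likely to notice discomfort. This is a fair reason to expect better capture than bare self-report by children. It still leaves reporting to the family's initiative.

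Third, participants and outcome assessor are blinded and both arms report in the same way. Equal under-capture would therefore mainly lower both counts and would not by itself bias the comparison. This stands. The damage is to the absolute rates and to the meaning of a low count.

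Three stronger readings are tempting, and the document supports none of them:

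- A reader might infer that families are deterred from reporting. That requires them to know that a report ends participation, and the article does not say they are told.
- A reader might infer that exclusion ends all contact, so that no event is followed to its end. The article speaks of exclusion from the study and is silent on follow-up of the event. Loss of the later course is possible, not established.
- A reader might infer that the reported event itself goes uncounted, or that the committee would see only its onset. Exclusion does not erase the report, and the article does not say what event data the committee receives.

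**Conclusion.** The point holds in a limited form. The article describes one unprompted route to adverse events, ties a report to exclusion, and describes two existing contacts without an enquiry. Under-counting is the likely direction, and the later course of a reported event may be lost.

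Its size cannot be derived from the document. The 7.2% bound follows from 0 of 40 with full capture. The 14% to 24% range rests wholly on an assumed capture of 50% to 30%, for which the article gives no basis.

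Separately, excluding children with an event does not sit with an analysis said to include everyone recruited, and the two sections must be reconciled. This is a cheap improvement to the harms data. It does not threaten the primary comparison through power alone.

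**What to change.** - Add one fixed adverse-event question, worded identically in both arms, to the weekly message and to the week-4 session. Record start, end and severity.
- Report solicited and spontaneous events separately, by arm.
- State that data collection continues after a reported event, including its course and the week-4 measurements.
- Reconcile the exclusion in the Adverse events section with the intention-to-treat statement in the Statistical analysis section.

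Whether a child continues the product after an event is a clinical matter and is not part of this change.

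Cost: one line in a message already sent, one question at a session already held, and a few fields on a form. The downside is that more minor, unrelated complaints will be recorded, and the harms figures may look slightly less favourable.
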